# Manipulation under anesthesia versus physiotherapy treatment in stage two of a frozen shoulder: a study protocol for a randomized controlled trial

**DOI:** 10.1186/s12891-017-1763-2

**Published:** 2017-10-11

**Keywords:** Frozen shoulder, Adhesive capsulitis, Manipulation under anesthesia, Physiotherapy

## Abstract

**Background:**

There is no consensus about the optimal treatment strategy for frozen shoulders (FS). Conservative treatment consisting of intra-articular corticosteroid infiltrations and physiotherapy are considered appropriate for most patients. However, with a conservative strategy, patients experience a prolonged rehabilitation period with a considerable amount of pain and disabilities in daily life. Also, at long term, a residual amount of pain and restriction of range of motion is frequently reported. Manipulation under anesthesia is a short and relative simple procedure with the potential to rapidly reduce symptoms and restore the range of motion. The objective of this trial is to evaluate the effectiveness of MUA followed by a PT program compared to a PT program alone, in the treatment of patients with a stage two FS. We hypothesize that the course of the disease can be shortened with MUA with a quicker functional recovery.

**Methods:**

This is a prospective, single center, randomized controlled trial. Eligible patients will be allocated to either the manipulation (MUA) group or the physiotherapy alone (PT) group. In the MUA group manipulation will be performed under interscalene block, directly followed by an intensive physiotherapy treatment protocol, with the goal to maintain the obtained range of motion. Patients allocated to the PT group are given advice and education and receive a written protocol to hand out to their physical therapist based on the recent guideline of the Dutch Shoulder Network for the treatment of frozen shoulders. Descriptive statistics will be used to describe the sample size, patients demographics, presence of diabetes mellitus, range of motion, duration of symptoms till randomization and will be presented for each treatment group. The SPADI is used as primary functional outcome parameter. Secondary outcome parameters are; OSS, NPRS, EQ-5D 3-L, passive range of motion, WORQ-UP, duration of symptoms, usage of analgesics and adverse events. A sample size of 41 subjects in each group was calculated. Follow up is planned after 1,3 and 12 months. The length of physiotherapy treatment in both groups is variable, depending on individual progression. Differences between groups in outcome parameters will be analysed using the linear mixed modelling and the restricted maximum likelihood ratio technique for estimating the model parameters.

**Discussion:**

Successful completion of this trial will provide evidence on the best treatment strategy for patients with a stage two frozen shoulder. The results of this study can lead to a better understanding for the role of manipulation in the treatment of frozen shoulders.

**Trial registration:**

This trial is registered in the Dutch Trial Register under the number NTR6182 on the 20th of February 2017.

## Background

Frozen shoulder (FS) is a common cause of shoulder pain and disability. It affects approximately 2-4% of the general population [1], with a peak incidence between the fifth and sixth decade. FS is slightly more frequent in women than in men, and the most important associated condition is diabetes [1, 2]. The pathophysiology of idiopathic FS is still poorly understood [3]. Idiopathic FS is characterised by a spontaneous onset of pain and stiffness of the shoulder, especially a loss of external rotation, without a prior traumatic event [4]. FS is traditionally divided in three stages [5]. Stage one is called the “freezing stage” and is characterised by severe pain and increasing stiffness. Stage two is the “frozen stage” with established stiffness and reduced pain at rest, but still painful at the end of the range of motion. In the third stage, the “thawing stage”, gradual improvement of motion occurs. Earlier studies considered it to be a self-limiting, reversible condition [5, 6]. Conservative treatment, most frequently consisting of physiotherapy (PT) and corticosteroid infiltrations, is considered appropriate for the majority of patients [4]. However, with conservative treatment residual pain is reported in up to 50% of patients and measurable restriction of motion in up to 60% [7, 8]. Functional limitations at long term occur in 6 - 16% of patients [9, 10]. Also, natural history studies suggest an average duration of 30.1 months [11]. Patients experience a prolonged rehabilitation period with a considerable amount of pain and disability in daily life. Their functional limitations can lead to absenteeism at work [12–14]. There are several invasive treatment procedures possible, like manipulation under anaesthesia (MUA), arthroscopic capsular release and hydrodilatation. However, good quality comparative studies concerning these procedures are scarce. Systematic reviews point to a lack of evidence, with no consensus about superiority of one of these procedures [11, 15–17].

Traditionally, manipulation under anaesthesia (MUA) is a well-established treatment for FS if conservative treatment fails [13, 18, 19]. MUA is a short and relative simple procedure by which capsular adhesions are torn apart by manipulation, with the potential to rapidly restore the range of motion and reduce symptoms within days after the procedure [20]. However, the role of MUA in the treatment of FS is still controversial because it might lead to serious complications in rare cases such as a humeral fracture, glenohumeral dislocation, and brachial plexus traction injury [21, 22]. Other potential complications are intra-articular damage to the cartilage, glenoid rim fractures, or rotator cuff tears [23]. On the other hand, rotator cuff integrity was maintained after MUA in the study of Atoun [24] and the reported complication rate in cohort studies and reviews of 0.5% is rather low [16, 20, 25].

There is only one randomized controlled trial, in which MUA is compared to conservative treatment. Kivimäki et al. conducted a randomized trial with 110 patients in which MUA in combination with a home exercise program was compared to a home exercise program alone [14]. A small difference regarding mobility and pain in favour of the manipulation group was found, but was considered clinically unimportant. However, 34% of patients were lost to follow up after 6 months, and only 3 patients of the manipulation group were available for follow up at 12 months. Therefore, no firm conclusions can be drawn based on that study. Moreover, the rehabilitation after MUA was far different from the physiotherapy protocol in the current study. In the study of Kivimäki et al., physiotherapy advice was given in two sessions and written instructions for a home exercise program were provided. We suppose that an initial period of one to 2 weeks of intensive physiotherapy treatment after MUA is essential to prevent recurrence of restrictions. Therefore, we advocate a more aggressive rehabilitation with intensive stretching and range of motion exercises in the first weeks after MUA to preserve the obtained range of motion.

In the current situation in our hospital, a variability in the threshold to decide for MUA between the different individual orthopaedic surgeons in the treatment of FS was noticed. This variability was also demonstrated in a survey among Dutch and Belgian orthopaedic surgeons [26]. In addition, we found that MUA was carried out most frequently at our hospital. In anticipation of the current protocol for an RCT, we reviewed our own results after manipulation in a retrospective cohort study. In 2 years, 89 patients were treated by manipulation for a FS. Eighty-five percent of the patients were satisfied with the procedure with good results. No complications were noticed. ([name] et al. *Acta orthopaedica Belgica* 2017, in press).

The objective of this trial is to evaluate the effectiveness of MUA followed by a PT program compared to a PT program alone in the treatment of patients with a stage two FS. We hypothesize that the course of the disease can be shortened with MUA with a quicker functional recovery and gain in range of motion and a subsequent faster return to work compared to physiotherapy treatment.

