### Intervention

Patients assigned to the MUA group will be scheduled for the intervention within approximately 2–6 weeks (generally within 2 weeks). MUA is performed by one orthopaedic surgeon (RB) at the recovery room under single shot interscalene brachial plexus block. The interscalene block is administered by the anesthesiologist using ultrasound guidance. Levobupivacaine 0.375% is used, and a ‘soak time’ of approximately 45 min is pursued. If necessary or desired by the patient, general anesthesia can be added. The scapula is indirectly stabilized by the supine position, a short lever arm and 90 degrees of elbow flexion is used to prevent fractures and brachial plexus traction injuries. The glenohumeral joint is forced through a full range of motion in a strict pattern: anteflexion - > abduction, external rotation in 90 degrees’ abduction- > internal rotation in 90 degrees’ abduction - > horizontal adduction with dorsal compression and external rotation in neutral. A recognizable tearing sound is typically present when dealing with a FS. This sequence can be repeated until full range of motion is acquired. Postoperative physiotherapy is started directly on the same day (within 4 h after MUA) to maintain the acquired full range of motion. People stay at the orthopaedic ward for one night. The first week after MUA, patients have to visit a physiotherapist on a daily basis. The physiotherapy treatment is individualized in the need of the particular patient and it’s possibilities in ROM and dysfunction after a long period of stiffness. Therapy will exist of mobilizations in all end ranges known in arthrokinematics of the shoulder which are the same used by the orthopedic surgeon during MUA. Mobilizations are applied in (Maitland) grade 3, 4 or even 5 if necessary. This means that end feel is reached even if painful. The target is to reach the same end range as reached by the orthopedic surgeon after MUA, or the best possible after anesthetics are worked out. It is continuously tried to be within the pain area of NRS 0 to 5 or even up to NRS 7 for a short period of time, but only then when the pain vanishes within one or 2 h after therapy. The goal is to give the maximum of stimulus which the patient can handle. Therefore, the frequency of therapy is high, but the period of inflammation after manipulation is respected. Patients are given a home exercise program to maintain ROM which they have to imbed in their daily activities. The exercises will mainly concern stretching in different angles with a total end range time of at least 2 min. After 2 weeks, if ROM is maintained, a general exercise program is applied to regain function of cuff and scapular muscles (using elastic exercise bands or halters) with the goal to return to normal shoulder girdle function.

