Secondary outcome measures consist of;Oxford Shoulder Score (OSS), which reflects both function and pain of the shoulder. The OSS is a patient reported questionnaire, which consist of 12 questions related to pain and function of the arm in daily life. Items are scored on a zero to four point scale. This leads to an OSS score between 0 (worst) and 48 (best) [30].Shoulder pain at rest, and during activity; Pain level will be determined using the The Numeric Pain Rating Scale (NPRS). The NPRS is a validated 11-point score to assess pain, which represents a valid measure of pain with a good construct validity. The NPRS ranges from zero to ten, in which zero expresses no pain and ten expresses the worst pain possible.Health related quality of life, determined using the three level EuroQol five-dimensional questionnaire (EQ-5D 3-L). The EQ-5D is a five question standardised questionnaire scoring on five domains: mobility, self-care, usual activities, pain/discomfort, and anxiety/depression. It also includes a VAS self rating health scale on which patients rate their health state (0 is worst imaginable health and 100 is best imaginable health) [31]Passive Range of Motion (ROM) is measured by a goniometer. Forward flexion and abduction in the standing position, external rotation measured with the arm held at the side and the elbow in 90° flexion. Internal rotation is estimated to which height the patient can reach on his back, appointed to the highest vertebral level of the wrist.The ability to work is evaluated by two questionnaires. The WORQ-UP is a patient reported questionnaire with 17 items of common physical tasks at work, scored on a five point scale [32]. Single item work ability Index is a single question whereby patients rate their ability to perform physical tasks at work on a ten point scale. Zero indicates no ability to perform work with any physical task at all. Ten indicates the best period in life to perform physical tasks at work [33–35]. Absenteeism at work is evaluated with a single question where patients register the amount of days absent at work past month due to complaints of the shoulder.Duration of symptoms is determined. Patients are asked to estimate the duration of symptoms in weeks from MUA or allocation to the PT group until almost full recovery.Two anchor questions will be asked regarding the change that is experienced since the start of treatment considering pain and daily functioning. This is reported on a seven-point scale. These questions are based on an advice to use them from the division shoulder and elbow from the Dutch Orthopaedic Society.Quantity of physiotherapy treatment sessionsUsage of analgesics (acetaminophen, NSAID’s or opioids)Number of repeated corticosteroid infiltrationsNumber of complications (infection, fracture, dislocation, neurovascular compromise, subsequent or intervention) will be registered and evaluated.

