Complications are counted by type and in total and will be analysed using Poisson regression analysis with a correction for overdispersion when appropriate. Treatment effects on complication rates will be expressed as MUA to PT rate ratios. Safety will be assessed by identifying and summarising adverse events collected throughout the study.

All estimated treatment effects will be accompanied by 95% confidence intervals and *p*-values.

Analysis will be performed by use of SPSS statistical package (IBM, version 18.0; SPSS, Chicago, Illinois).

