## Discussion

There is no consensus in the literature which patients with a FS will benefit most from MUA [11, 15, 17]. MUA is considered as an option when conservative treatment fails. However, the optimal timing of MUA is unknown [12, 38]. Furthermore, timing between the onset of symptoms and MUA can be a crucial parameter when the effectiveness of MUA is evaluated. In a condition that is mainly self-limiting, shortening of the duration of symptoms is probably more interesting than the end result at long term. Theoretically, the biggest advantage of manipulation is obtained when manipulation is done early. It could be suggested that early manipulation could lead to over-treatment in patients with a mild and natural course of the disease. Even more, early manipulation in stage one (the painful inflammatory phase) is sometimes considered to be counterproductive and can lead to recurrence of symptoms [12]. On the other hand, a high threshold for MUA, or late intervention, can lead to an unnecessarily long duration of complaints. In a retrospective study, Vastamäki et al. considered between 6 and 9 months after the onset of symptoms as the most optimal period for manipulation [12]. However, only a general comparison between group A (between 6 and 9 months) and group B (the others, including before 6 months and after 9 months) was presented. In our opinion, this is not convincing evidence to draw firm conclusions about the optimal timing. Although clear cut-off values between different stages of a FS are lacking, we decided to define in- and exclusion criteria as described above to select patients with a FS in stage two. The exclusion criteria NRS ≥ 7 is debatable because the lack of cut-off values in the literature. We added the important parameter that pain must be diminished compared to the maximum pain in stage one. Hereby, we try to prevent over treatment and recurrence after too early manipulation. Furthermore, with this study protocol, unnecessarily long duration of symptoms are potentially avoided. With the results of this study, we aim to increase our knowledge about the efficacy of MUA compared to physiotherapy treatment. We aim to solve a part of the uncertainty of the indication of MUA, and the safety of MUA is critically assessed.

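### The listed complication types leave out two of the six MUA harms the protocol names, and non-neurovascular anaesthetic harms, so the modelled MUA to PT rate ratio is likely to under-count harms of MUA

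*Protocol article*

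**What the plan says.** The Background of the protocol article lists harms of MUA in two sentences. The first speaks of "serious complications in rare cases such as a humeral fracture, glenohumeral dislocation, and brachial plexus traction injury". The second adds: "Other potential complications are intra-articular damage to the cartilage, glenoid rim fractures, or rotator cuff tears". It then offers reassurance, citing one study in which "rotator cuff integrity was maintained after MUA" and stating that "the reported complication rate in cohort studies and reviews of 0.5% is rather low".

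Under Outcome measures, the last secondary outcome is the number of "complications (infection, fracture, dislocation, neurovascular compromise, subsequent or intervention) will be registered and evaluated". The final item in that parenthesis is garbled and probably means re-intervention.

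The Statistical analysis section says: "Complications are counted by type and in total and will be analysed using Poisson regression analysis". Results are to be given as MUA to PT rate ratios. A separate sentence there says that adverse events collected during the study will be identified and summarised; it states no between-group effect measure for them.

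Under Intervention, every MUA patient receives an interscalene block, and "If necessary or desired by the patient, general anesthesia can be added". The Discussion says that "the safety of MUA is critically assessed".

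**The concern.** The outcome that is modelled should be able to register the harms that the protocol itself expects from the procedure. A cuff tear or cartilage injury treated without re-intervention has no place among the five types. Neither does an anaesthetic harm that is not neurovascular. If the list is followed as written, these events do not reach the per-type counts or the total, and so do not reach the rate ratio. Two of the missing types are harms that the protocol attributes to manipulation, and the block and general anaesthesia are given by protocol only in the MUA arm. Omission would therefore tend to make MUA look safer in the one safety result that has an effect measure, which fits poorly with the aim stated in the Discussion. With so few complications expected, how each one is classified matters.

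**Working it through.** **1. Setting the two lists side by side.**

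| Harm of MUA named in the Background | Matching type in Outcome measures |
|---|---|
| Humeral fracture | fracture |
| Glenohumeral dislocation | dislocation |
| Brachial plexus traction injury | neurovascular compromise |
| Glenoid rim fracture | fracture |
| Cartilage damage | none |
| Rotator cuff tear | none |

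Four of six have a type and two do not. For the anaesthetic, nerve injury from the block fits neurovascular compromise; other harms of the block or of general anaesthesia have no type.

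**2. Group size.** The plan gives 41 per group for a difference of 13 SPADI points, SD 17, power 90%, alpha 0.05 (taken as two-sided) and 10% dropout. The normal formula gives n = 2 × (1.960 + 1.282)² × 17² / 13² = 36, and 36/0.9 = 40. The t-test version gives 36.9, so 37, and 37/0.9 = 41.1. The plan's 41 is reproduced and is used below as the size of the MUA arm.

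**3. Expected complications at the cited overall rate of 0.5%.** 41 × 0.005 = 0.2 events. The chance of at least one is 1 − 0.995⁴¹ = 19%. This rate covers complications overall and is not a rate for the omitted types.

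**4. Range for the omitted harms.** The documents give no rate, so these are assumptions:

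| Assumed rate per patient | Expected MUA events, 41 × p | Chance of at least one, 1 − (1 − p)⁴¹ |
|---|---|---|
| 1% | 0.4 | 34% |
| 2% | 0.8 | 56% |
| 5% | 2.1 | 88% |

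**5. Effect of one uncounted event** (exact Clopper-Pearson 95% intervals).
- Counted: 1/41 = 2.4%, interval 0.06% to 12.9%. The lower limit is 1 − 0.975^(1/41).
- Not counted: 0/41 = 0%, interval 0% to 8.6%. The upper limit is 1 − 0.025^(1/41).

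**6. Effect on the between-group inference.** With no events in PT and k in MUA, the two-sided conditional binomial p-value is 2 × 0.5^k. One event gives p = 1.0, five give 0.063 and six give 0.031; Fisher's exact test gives 0.055 for five and 0.026 for six. At least six events against none are needed for p < 0.05, so one reclassified event changes the reported rate but not the inference from the ratio.

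**The case against.** A reader might infer that the safety comparison can err only in favour of MUA. The documents do not support that, for four reasons.

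- **Open capture exists.** The abstract lists adverse events as an outcome, the Statistical analysis section summarises them, and Monitoring and quality assurance obliges all investigators to report them. None of this is restricted by type. The gap concerns one modelled count, not all safety data.
- **Some omitted harms may already have a type.** Block-related nerve injury fits neurovascular compromise. If the garbled last item means re-intervention, a cuff or cartilage lesion that is operated on is counted.
- **PT events can be missed too.** Repeat corticosteroid injection is described for the PT arm, and its non-infectious harms also have no type. Patients who cross over from PT to MUA are analysed as PT, so a cuff or anaesthetic harm in one of them would be lost from the PT count.
- **The parenthesis may be illustrative.** The analysis sentence does not refer back to it, and the Background itself calls cuff tears and cartilage damage potential complications.

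The first three stand and limit the claim to a likely direction. The fourth stands only in part. The parenthesis has no wording that marks it as examples, whereas the first harm list in the Background does. If it is illustrative, the line between a complication and any other adverse event is not drawn, and the same short clarification is needed.

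The article also condenses a fuller protocol that may define complications in more detail. But it does print a list, and that list does not match its own Background. Finally, the hospital's earlier series reported no complications in 89 manipulated patients. This suggests low counts, but the article does not say what was counted as a complication there.

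**Conclusion.** The mismatch is real and minor. Two of the six harms that the protocol attributes to MUA, and non-neurovascular harms of the anaesthetic, have no type in the complication outcome. On a literal reading they would be described among adverse events but left out of the rate ratio, unless they led to re-intervention. The ratio is then likely, not certain, to under-count harms of MUA. This rests on two assumptions: that the list is applied as printed, and that the analysed complications are those on the list.

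The number of events missed is unknown, because no rate is given for the omitted harms. One such event would move the reported MUA rate from 2.4% to 0% in 41 patients, with widely overlapping intervals and no change in the test result. The outcome is secondary, and precision would be poor even with a complete list: no events in 41 patients still leaves an upper limit of 8.6%. The case for change therefore rests on correct classification, not on power.

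**What to change.** In Outcome measures, add three counted types: new rotator cuff tear, intra-articular (cartilage) injury, and complication of anaesthesia or injection. Define them identically in both arms, count events found at the scheduled evaluations or on imaging done for clinical reasons, and add no imaging. Alternatively, state in Statistical analysis that the modelled total includes all treatment-related adverse events. With either option, record how each event was found and reword the garbled last item of the list.

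The cost is a line of protocol text and up to three extra categories on the complication form. Sample size, visits and clinical care are unchanged. There are two small downsides. The MUA count may look less favourable. Detection may also be more frequent after MUA, because those patients may be imaged more readily; the record of how each event was found makes this visible. Without added imaging, clinically silent lesions will mostly remain unfound, so the change corrects the classification of events that come to light and does not measure the true incidence.
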